### Measures

Table 1 provides an overview of the study variables and their assessment moments. We adapted the wording of some items from the original questionnaires to make them suitable for mothers with low educational levels, using specific guidelines for Dutch texts [61]. Following these guidelines, we tried to keep items short, use an active voice, and avoid using difficult words. For example the phrase ‘I do not do things that I know my child wants me to do,’ was rephrased as ‘I do not do what my child wants me to do.’ With the exception of life events, mothers report on all measures about the last month.

**Table 1 Tab1:** Overview of Study Variables

Outcome	Measure	T1	T2	T3	T4	Reference
Primary outcomes						
Parental self-efficacy	Parenting Stress Index	x	x	x	x	[68]
Levels of perceived stress	Perceived Stress Scale	x	x	x	x	[69]
Parental anger	Parental Anger Scale	x	x	x	x	[70]
Post-traumatic stress symptoms	Post-Traumatic Stress Disorder Checklist – Civilian	x	x	x	x	[65]
Secondary outcomes						
Risk for child maltreatment	Instrument for early identification of Parents At Risk for child Abuse and Neglect	x			x	[54]
Parenting (Rejection, Hostility, Attention, Affection)	Comprehensive Parenting Behavior Questionnaire	x			x	[71]
Potential moderators						
Child temperament (Soothability, Negative emotionality)	Revised Infant Behavior Questionnaire	x				[72]
	Very Short Form of the Revised Infant Behavior Questionnaire					[73]
Life events	Parenting Stress Index	x^a^			x^b^	[68]

*Note.*
^a^ = life events experienced in the past 12 months, ^b^ = life events experienced during the study

### Primary outcome measures

#### Parental self-efficacy

Mothers report on feelings of self-efficacy on the shortened Sense of Competence subscale of the Parenting Stress Index [68]. Mothers rate nine items, such as ‘I feel that I am not very good at being a parent’ on a six-point scale ranging from 1 (*I totally disagree*) to 6 (*I totally agree*). All items are reverse coded such that higher scores indicate higher levels of parental self-efficacy.

#### Levels of perceived stress

Mothers report on feelings of stress on the ten-item-version of the Perceived Stress Scale (PSS-10 [69]). This is a widely-used questionnaire that assesses the degree to which respondents experience situations in one’s life as stressful, that is, unpredictable, uncontrollable and overwhelming, in the past month. The internal consistency of the PSS-10 varies between α = .74 and α = .91 [74]. Mothers rate ten items, such as ‘In the last month, how often have you found that you could not cope with all the things that you had to do?,’ on a five-point scale ranging from 1 (*never*) to 5 (*very often*). Four items are reverse coded such that higher scores indicate higher levels of perceived stress.

#### Parental anger

Mothers report on parental anger on the ‘expression’-subscale of the Parent Anger Scale (PAS [70]). This questionnaire assesses anger experience in the parent-child context. The PAS expression subscale has high internal consistency (α = .95) and correlates to other measures of negative affect and discipline strategies [75]. Mothers rate 11 items such as ‘I get so angry with my child, that I scream or yell at my child’ on a seven-point scale ranging from 0 (*never*) to 6 (*several times a day*).

#### Post-traumatic stress symptoms

Mothers report on post-traumatic stress symptoms on the six-item version of the abbreviated PTSD checklist – civilian (abbreviated PCL-C [65]). This is a more extensive version of the checklist that nurses will use as a screening tool in the manualized component on recognition of post-traumatic stress symptoms. The abbreviated PCL-C is an adequate screening instrument for PTSD, with a sensitivity of .95 and a specificity of .57 in women [65]. Mothers rate the extent to which six symptoms, such as ‘repeated, disturbing memories, thoughts or images of the stressful experience,’ occurred on a five-point scale ranging from 0 (*not at all*) to 4 (*extremely*).

In order to measure nurses’ ability to recognize post-traumatic stress symptoms in mothers, nurses report to what extent they think a mother suffers from post-traumatic stress symptoms on a five-point scale ranging from 0 (*not at all*) to 4 (*extremely*). We will correlate mothers’ and nurses’ answers with each other as an indication of how adequately nurses recognize post-traumatic stress symptoms in mothers.

### Secondary outcome measures

#### Parenting practices

Mothers report on four dimensions of parenting practices on the following subscales of the Comprehensive Parenting Behavior Questionnaire (CPBQ [71]): Rejection (2 items, such as ‘Sometimes I am really fed up with my child, and this clearly shows’); Hostility (4 items, such as ‘Sometimes I can be harsh when my child is really annoying’); Attention (4 items, such as ‘I regularly play or talk with my child for at least 5 min, with our attention focused on one other, just for fun’); and Affection (4 items, such as ‘I often cuddle my child’). All items are rated on a five-point scale ranging from 1 (*totally not applicable*) to 5 (*completely applicable*). In the hostility subscale, one item is reverse-coded such that higher scores indicate higher levels of hostility.

#### Risk for child maltreatment

Mothers report on their risk for child maltreatment on the Instrument for early identification of Parents At Risk for child Abuse and Neglect (IPARAN [54]). This is the same questionnaire that youth health care centers use to screen families for the Supportive Parenting program. Mothers rate nine items, such as ‘I can get so angry that I lose control’ on a scale ranging from 1 (*always*) to 4 (*never*) and answer seven yes/no items, such as ‘I feel that my parents/carers hit me too much as a child.’ The items differ in their scoring and answers correspond with scores of either 0, 0.1, 0.2, 0.3, 0.5, or 1 (for more details, see [76]). The IPARAN has shown to adequately predict future reports of child maltreatment [76]. Youth care centers use a simplified rating system where answers are scored as 0, 0.5, 1, 1.5, or 2. Families where at least one parent scores ≥3 are offered the Supportive Parenting program.

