**Methods:**

We will conduct a randomized controlled trial among 398 mothers enrolled in a Dutch home visiting program targeting families at risk for child maltreatment. Mothers in the experimental group will receive the manualized components in two consecutive home visits, while mothers in the control group will receive regular home visits (care as usual). Mothers will fill out questionnaires at four time points: before and after each of the two home visits. Outcome variables include the four targeted risk factors parental self-efficacy, perceived stress, parental anger, and (recognition of) post-traumatic stress symptoms, as well as parenting practices (e.g., rejection and affection), and risk for child maltreatment.

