## Methods/design

### Design

We will conduct a randomized controlled trial in the context of an existing Dutch home visiting program aimed at the prevention of child maltreatment (Supportive Parenting, in Dutch “*Stevig Ouderschap*” [54]). Mothers will be randomly assigned to receive either two consecutive home visits that include the additional manualized components (i.e., manualized home visiting), or to receive standard home visits (i.e., care as usual) with a 1:1 allocation using a computerized random number generator.

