### Sample size calculation

As we will compare two active conditions, we expect to find relatively small effects. More specifically, we expect moderate effects on the targeted risk factors (i.e., our more proximal outcome measure) and a small effect on mothers’ risk for child maltreatment (i.e., our more distal outcome measure). Previous additive studies (i.e., studies in which effects of an intervention are compared to effects of the same intervention with one or more additional components) also demonstrated small to moderate average effect sizes for interventions with added components [77]. Our sample of *N =* 398, with two groups and one-sided tests at α = .05 provide us with a power (1 – β) of .80 to detect effects of *d* = .25 [78]. Following the guidelines of Fritz and MacKinnon [79], our sample size will also allow for sufficient power to detect mediation effects when using mediation analyses based on bootstrapping.

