### Analyses

Prior to analyzing the data, missing data will be handled with multiple imputation. To test whether adding manualized components ameliorates four risk factors (i.e., low parental self-efficacy, high levels of perceived stress, parental anger, and post-traumatic stress symptoms), improves parenting practices, and reduces risk for child maltreatment, we will conduct multivariate analyses of covariance (MANCOVA) and an analysis of covariance (ANCOVA) respectively, with baseline scores (T1) as the covariates, with data of T2, T3, and T4 for the risk factors and data of T4 for parenting practices and risk for child maltreatment as dependent variables.

To test whether amelioration of the targeted risk factors by the added components explains (i.e., mediates) reduced risk for child maltreatment we will conduct a mediation analysis using the PROCESS Macro in SPSS [80]. This macro computes 95% confidence intervals of the indirect effects based on 1000 bootstrap samples. Intervals that do not include 0 indicate a mediation effect.

To test who benefits most from the manualized components we will test whether condition × child, maternal, or family characteristic interaction effects predict ameliorated risk factors and reduced risk for child maltreatment. Putative moderators include mothers’ baseline levels of each of the four risk factors (maternal characteristics), children’s temperament (child characteristic), and the number of life events in the past year and during the study (family characteristic).

We will conduct interim descriptive analyses for our progress annual reports for the study funder. However, no interim analyses that answer the research questions of this study will be conducted. The full protocol, anonymized dataset, and the statistical code that will be used in this study will be available upon motivated request after publication of the results in a peer-reviewed paper.

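### IPARAN mixes at least one fixed childhood-history item with changeable items, so splitting its T1 covariate is a free but modest gain in precision, and the last-month sentence needs correcting

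*Protocol article*

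**What the plan says.** All references are to the protocol article.

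- **Risk for child maltreatment:** IPARAN has nine rated items and seven yes/no items, with unequal item scores. The example of a rated item concerns losing control when angry. The example of a yes/no item is "I feel that my parents/carers hit me too much as a child".
- **Participants:** a history of child maltreatment is named as one reason why a family screens as elevated risk on this instrument.
- **Measures:** "With the exception of life events, mothers report on all measures about the last month". Table 1 lists IPARAN as a secondary outcome, measured at T1 and T4 only.
- **Analyses:** the T4 score is the dependent variable of an ANCOVA "with baseline scores (T1) as the covariates". No sub-score of IPARAN is described.
- **Sample size calculation:** 398 mothers, "with two groups and one-sided tests at α = .05", "provide us with a power (1 – β) of .80 to detect effects of" d = .25. A small effect is expected on maltreatment risk.

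**The concern.** Two things do not fit.

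First, an item about the mother's own childhood cannot refer to the last month. The recall statement is therefore wrong for at least this item.

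Second, the T4 total is the sum of a part that hardly moves between T1 and T4 and a part that the visits are meant to move. The nearly fixed part predicts itself with a slope near 1. The changeable part predicts itself with a slope near its retest correlation. A single T1 score as covariate forces one compromise slope on both, and the misfit stays in the residual variance.

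The stake is precision. IPARAN is the only measure of maltreatment risk in Table 1 and the outcome of the mediation analysis, and the expected effect on it is small. Any effect confined to the changeable items is also smaller when expressed in standard deviations of the total.

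**Working it through.** **1. The plan's own figure.** The Design section gives 1:1 allocation, so 398 mothers are 199 per arm. With one-sided α = .05 and d = .25, the normal approximation is Φ(.25·√(199/2) − 1.645) = .802. The noncentral t gives .801 at 199 per arm and .799 at 198. The stated N and power reproduce, with no covariate in the calculation.

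**2. Recall window.** Measures exempts only life events from the one-month window. The IPARAN item is about childhood. Both statements cannot hold, and no assumption is needed to see it.

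**3. Model for the covariate.** Write the IPARAN total as a history part plus a changeable part, with total variance 1 at both T1 and T4 and the two parts uncorrelated. Let f be the history share of the variance, r_s the T1-T4 correlation of the history part, and r_d that of the changeable part. None of the three is in the document, so all are assumptions.

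- Residual variance with the T1 total: V_tot = 1 − (f·r_s + (1−f)·r_d)²
- Residual variance with two T1 sub-scores: V_split = 1 − f·r_s² − (1−f)·r_d²
- Difference: V_tot − V_split = f(1−f)(r_s − r_d)², which is never negative and is zero when r_s = r_d.

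**4. Numbers.** The saving is 1 − V_split/V_tot. The last column is 398·V_split/V_tot, the number of mothers who would give the same precision with the split.

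| f | r_s | r_d | V_tot | V_split | Saving | Equivalent N |
|---|---|---|---|---|---|---|
| .10 | 1.0 | .5 | .6975 | .6750 | 3.2% | 385 |
| .30 | 1.0 | .5 | .5775 | .5250 | 9.1% | 362 |
| .50 | 1.0 | .5 | .4375 | .3750 | 14.3% | 341 |
| .60 | 1.0 | .4 | .4224 | .3360 | 20.5% | 317 |
| .30 | .9 | .5 | .6156 | .5820 | 5.5% | 376 |
| .10 | .9 | .6 | .6031 | .5950 | 1.3% | 393 |
| .20 | .8 | .6 | .5904 | .5840 | 1.1% | 394 |
| .30 | .8 | .7 | .4671 | .4650 | 0.4% | 396 |

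A retest correlation of only .3 for the changeable items would raise the top slightly: at f = .60 and r_s = 1, .6·.4·.7²/.4816 = .1176/.4816 = 24%.

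A simulation at f = .5, r_s = 1, r_d = .5 with 199 per arm found both estimators unbiased and a variance ratio of .866, against .857 by formula. Under selection on a high T1 total (top 6.5%), the ratio was .86 to .95.

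**5. Correlated parts.** If the parts correlate, the result depends on how history relates to the changeable part at T4. With shares of 30-60%, correlations of 0-.4, r_d of .4-.6 and r_s of .9-1.0, the saving is about 4-30% if the cross-correlation does not decay from T1 to T4, and about 2-20% if it decays with the retest correlation. The 30% end needs childhood history to predict T4 current state as well as it relates to T1 current state.

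**6. Dilution and power.** Suppose d = .25 holds on the changeable items only and r_s = 1. The d on the total is .25·√(1−f), which is .209 at f = .3 and .177 at f = .5. Power at 199 per arm, one-sided α = .05:

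| f | r_d | Unadjusted | T1 total | Split |
|---|---|---|---|---|
| .3 | .5 | .671 | .864 | .892 |
| .5 | .5 | .547 | .846 | .892 |
| .3 | .3 | .671 | .783 | .834 |
| .5 | .3 | .547 | .750 | .834 |

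The planned T1 adjustment already recovers most of the loss. The split adds about 3 to 8 percentage points in these cases.

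**The case against.** The strongest reply is that nothing in the analysis is wrong. ANCOVA of T4 on T1 is standard and unbiased under randomisation, and IPARAN is secondary. That stands: the point is about efficiency, not validity.

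A second reply is that the article speaks of T1 baseline scores and never says that the IPARAN total is the only covariate, and that a fuller plan may specify more. This also stands in part. One T1 score per outcome is the natural reading, but it is a reading.

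A third reply is that the size has no basis in the document. Only one childhood item among 16 is shown, the other six yes/no items are not described, item weights differ, and the item is phrased as a feeling, so answers may shift even though the event cannot. All of this stands. It is why the range must reach down to well under 1%.

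A reader might infer from the dilution figures (.177 to .209) that 398 mothers are too few for this outcome. The document does not support that. Those figures are before adjustment while the plan adjusts, they assume that the effect is confined to the changeable items, and the power statement gives d = .25 without that restriction. A reader might also infer a saving of 30%, but that figure rests on a cross-correlation that does not decay, for which the document gives no ground.

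What the replies do not remove is the contradiction over the recall window, and the fact that separate slopes cannot cost more than one degree of freedom out of about 395.

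**Conclusion.** The point holds as a free efficiency improvement plus a wording correction. The childhood item contradicts the one-month recall statement; that is certain from the text. Splitting the T1 covariate lowers residual variance by an amount that the document does not determine: under 1% to about 20% for assumed history shares of 10-60%, r_s of .8-1.0 and r_d of .4-.7 with uncorrelated parts. Within that range it is about 3% at a 10% share and 14% at a 50% share when r_s = 1 and r_d = .5. The gain disappears if both parts are equally stable. The planned ANCOVA remains valid, and the stated N and power stand.

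**What to change.** Before the data are seen:

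1. List which IPARAN items are history items.
2. Keep the T4 IPARAN total as outcome, and replace the single T1 score by two T1 covariates: the history-item score and the score of the remaining items.
3. Add a supportive analysis of the T4 score of the changeable items alone, labelled as supportive.
4. Correct the recall sentence in Measures so that it no longer covers the IPARAN childhood content.

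The cost is one degree of freedom, one extra analysis and one sentence. The items are already collected at T1 and T4, and recruitment is reported as ongoing, so no extra data or mothers are needed.

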### Potential moderators

#### Child’s temperament

Mothers report on two dimensions of their child’s temperament, i.e., soothability and negative emotionality. Mothers rate child soothability on 18 items, such as ‘when singing or talking to your baby, how often did s/he soothe immediately’, from the Revised Infant Behavior Questionnaire (IBQ-R [72]). Half of the items are reverse-coded such that higher scores indicate that children are easier to soothe. The internal consistency of the soothability subscale varies between α = .81 and α = .83 [72]. Mothers rate child negative emotionality on 12 items from the Very Short Form of the IBQ-R (IBQ-R VSF [73]) that were derived from the sadness, distress to limitations, and fear subscales of the original IBQ-R, such as ‘at the end of an exciting day, how often did your baby become tearful.’ The internal consistency of the negative emotionality subscale varies between α = .72 and α = .88 [73].

The original subscales use a seven-point scale ranging from 1 (*never*) to 7 (*always*). However, to accommodate for mothers with low educational levels we use four of the original answer categories for both scales (*almost never, less than half of the time, more than half of the time, almost always*). We chose to use four original response options and leaving three out, rather than combining options, to ensure that scores can be compared to scores in other studies using these measures.

#### Life events

Mothers report how many life events happened to them in the past 12 months and during the study on the ‘life events’-subscale of the Parenting Stress Index (PSI [68]). This subscale consists of thirty yes/no-items such as ‘I got fired/I quit my job’ or ‘I had a miscarriage.’

As most of the questionnaires that we used are copyright protected, we will not publish the data collection forms.

### Protection of data privacy

Data will be stored at secured servers of the University of Amsterdam and will only be accessible for researchers on this project. During the data collection process, participants’ names and contact information will be stored in a separate password-secured file that is only accessible for the researchers directly involved in this study. After data collection is complete, the contact information of participants who give consent to be contacted for future research will be stored in an encrypted file and will only be accessible for the research data manager. Contact information of participants who do not give consent to be contacted for future research will be deleted after data collection is complete.

### Sample size calculation

As we will compare two active conditions, we expect to find relatively small effects. More specifically, we expect moderate effects on the targeted risk factors (i.e., our more proximal outcome measure) and a small effect on mothers’ risk for child maltreatment (i.e., our more distal outcome measure). Previous additive studies (i.e., studies in which effects of an intervention are compared to effects of the same intervention with one or more additional components) also demonstrated small to moderate average effect sizes for interventions with added components [77]. Our sample of *N =* 398, with two groups and one-sided tests at α = .05 provide us with a power (1 – β) of .80 to detect effects of *d* = .25 [78]. Following the guidelines of Fritz and MacKinnon [79], our sample size will also allow for sufficient power to detect mediation effects when using mediation analyses based on bootstrapping.

### Analyses

Prior to analyzing the data, missing data will be handled with multiple imputation. To test whether adding manualized components ameliorates four risk factors (i.e., low parental self-efficacy, high levels of perceived stress, parental anger, and post-traumatic stress symptoms), improves parenting practices, and reduces risk for child maltreatment, we will conduct multivariate analyses of covariance (MANCOVA) and an analysis of covariance (ANCOVA) respectively, with baseline scores (T1) as the covariates, with data of T2, T3, and T4 for the risk factors and data of T4 for parenting practices and risk for child maltreatment as dependent variables.

To test whether amelioration of the targeted risk factors by the added components explains (i.e., mediates) reduced risk for child maltreatment we will conduct a mediation analysis using the PROCESS Macro in SPSS [80]. This macro computes 95% confidence intervals of the indirect effects based on 1000 bootstrap samples. Intervals that do not include 0 indicate a mediation effect.

To test who benefits most from the manualized components we will test whether condition × child, maternal, or family characteristic interaction effects predict ameliorated risk factors and reduced risk for child maltreatment. Putative moderators include mothers’ baseline levels of each of the four risk factors (maternal characteristics), children’s temperament (child characteristic), and the number of life events in the past year and during the study (family characteristic).

We will conduct interim descriptive analyses for our progress annual reports for the study funder. However, no interim analyses that answer the research questions of this study will be conducted. The full protocol, anonymized dataset, and the statistical code that will be used in this study will be available upon motivated request after publication of the results in a peer-reviewed paper.

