### Study aims

In this study, we will test (1) whether manualized components designed to target four key risk factors for child maltreatment (low parental self-efficacy, stress, parental anger, and post-traumatic stress symptoms) indeed ameliorate these risk factors; (2) whether adding these manualized components to a home visiting program improves parenting practices and reduces the risk for child maltreatment; (3) whether any effect of the manualized components on reduced risk for child maltreatment can be explained (i.e., is mediated) by amelioration of the four targeted risk factors; (4) whether some mothers benefit more from the manualized components than other mothers in terms of ameliorated risk factors and reduced risk of child maltreatment.

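### The trial is sized on one one-sided comparison, but the four primary risk factors are tested by MANCOVA, which has no direction, so the stated power does not apply to it

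*Protocol article*

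**What the plan says.** All places are in the protocol article.

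- **Study aims.** Aim 1 is directional and names each factor: whether the components "indeed ameliorate these risk factors", that is, low parental self-efficacy, stress, parental anger and post-traumatic stress symptoms.
- **Measures, Table 1.** These four stand under "Primary outcomes", each measured at T1 to T4.
- **Sample size calculation.** The 398 mothers, "with two groups and one-sided tests at α = .05 provide us with a power (1 – β) of .80" "to detect effects of *d* = .25". That is one standardized difference and one comparison. The section expects moderate effects on the risk factors but gives no figure for them.
- **Design.** Two arms, "with a 1:1 allocation using a computerized random number generator".
- **Analyses.** MANCOVA is used for the sets of outcomes and ANCOVA for maltreatment risk, with T1 scores as covariates, "with data of T2, T3, and T4 for the risk factors and data of T4 for parenting practices and risk for child maltreatment". The section does not say whether the four factors and three time points enter one model or several, and it names no time point as primary.

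**The concern.** The aim, the sample size and the test do not fit together. The aim asks whether each factor gets better. The sample size assumes a one-sided test of one difference. The named test asks only whether the two mean vectors differ in any way. A MANCOVA with two groups is Hotelling's T², a quadratic form: reversing the sign of every effect leaves it unchanged, and it has no one-sided version.

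Two things are at stake. The .80 in the sample size section is not the power of the test that will be run. And a significant primary result would not by itself say that the factors improved. If the factors are pooled in one model, it would not say which factor moved either. T2 and T3 fall after one visit with the components and T4 after both, yet the omnibus test treats them alike.

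**Working it through.** **1. The plan's own figure.** Inputs from the article: d = .25, one-sided α = .05, power .80, allocation 1:1.

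Normal approximation: n per arm = 2(z.95 + z.80)²/d² = 2(1.645 + 0.842)²/.0625 ≈ 198, or 396 in total. With the exact noncentral t, n = 199 per arm, or **398**, with noncentrality .25 × √(199/2) = 2.49 and power .801. The stated size is reproduced, but only as a one-sided t-test of a single outcome. The same test two-sided has power .70, and 506 mothers would be needed for .80.

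**2. What the MANCOVA does.** For p dependent variables and q covariates, the test statistic follows a noncentral F with p and N − 2 − q − p + 1 degrees of freedom and noncentrality

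λ = (n/2) · δ′R⁻¹δ,

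where δ holds the standardized differences and R their correlations. Because δ enters twice, δ and −δ give the same λ.

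Take p = 12, q = 4, N = 398, so the denominator has 398 − 2 − 4 − 12 + 1 = 381 degrees of freedom. The article gives no correlations. I assume r = .3 to .5 between factors and t = .4 to .7 between times, with R the product of the two equicorrelated structures. No credit is taken for variance explained by baseline. Then:

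- all four factors shifted by .25 at all times, in either direction: λ = 99.5 × .0625 × 4/(1 + 3r) × 3/(1 + 2t)
- one factor better and one worse by .25, the other two unchanged: λ = 99.5 × .0625 × 2/(1 − r) × 3/(1 + 2t)

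| r | t | λ, all | Rejection: all better, or all worse | λ, mixed | Rejection: one better, one worse |
|---|---|---|---|---|---|
| .3 | .4 | 21.8 | .89 | 29.6 | .97 |
| .3 | .7 | 16.4 | .76 | 22.2 | .90 |
| .5 | .4 | 16.6 | .76 | 41.5 | .997 |
| .5 | .7 | 12.4 | .61 | 31.1 | .98 |

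In every row the test rejects more often for the mixed result than for uniform benefit.

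**3. Other readings of the sentence.**

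- *One MANCOVA per time point* (p = 4, 389 denominator degrees of freedom). Rejection for all factors shifted by .25 is .83 at r = .3 and .71 at r = .5, the same for benefit and harm. No factor is identified, and three tests are run.
- *One MANCOVA per factor over T2 to T4.* This does identify the factor. But four tests without direction are run, with no adjustment stated.

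**4. Power of the replacement at the first Holm step,** .05/4 = .0125, with 398 mothers:

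- d = .25, no baseline gain: .49 (about .50) two-sided, .60 one-sided.
- d = .25, T1 correlation .6 (assumed): effective d = .25/√(1 − .36) = .3125, giving .73 two-sided.
- d = .5 (an assumed reading of moderate), two-sided, no baseline gain: .99 with 398 mothers, and .97 with 318, which is 398 after an assumed 20% loss.

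**The case against.** MANCOVA is a recognised global test for correlated outcomes. The authors would presumably report adjusted means, so the direction of each effect would be visible. The article expects no adverse effects, so harm and mixed results are stress cases rather than forecasts. A single 12-variable model is not stated, and with one model per factor the identification problem disappears. Rules for follow-up tests are commonly left to a fuller plan.

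Much of this stands, and it limits the point. Showing the means does not, however, turn an omnibus p-value into a test of improvement. And no reading of the sentence makes the stated one-sided power apply to the stated test.

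A reader might go further in three ways that the document does not support:

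- *That the mediation aim needs a factor-by-factor follow-up to the MANCOVA.* It does not. The PROCESS analysis produces its own indirect effects and bootstrap intervals.
- *That the plan carries a particular inflated false-positive rate from univariate follow-up tests.* The article describes no such tests, so a rate would belong to a procedure the reader had supplied.
- *That uniform harm would be declared significant almost always.* On the assumptions above it is .61 to .89. Higher values need a further assumption about baseline correlation.

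The limitations section restricts conclusions to the four components combined. That concerns which component caused an effect, not which outcome improved, so it does not answer the point.

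**Conclusion.** The point holds as a mismatch between three things the article fixes: a directional aim on four primary outcomes, a sample size for one one-sided comparison, and an omnibus test without direction. The 398 is correct for the test it was computed for, but that is not the test named for the primary outcomes.

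The loss of direction is exact and needs no assumption. The rejection rates rest on the 12-variable reading, the assumed correlations, no baseline gain and no missing data. That a significant result fails to identify a factor holds if the factors share a model, whether one model overall or one per time point. With one model per factor, the remaining problem is four direction-blind tests without a stated adjustment.

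**What to change.** Make the primary analysis one model per risk factor: ANCOVA at T4, or a repeated-measures mixed model with the T4 condition contrast, with T1 as covariate. Apply Holm over the four factors, report estimates with 95% intervals, and treat T2 and T3 as supportive. State the sidedness explicitly. If it stays one-sided, state the favourable direction for each scale, because higher is better for self-efficacy and worse for perceived stress. Restate the power in the sample size section for this test.

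The change is to analysis wording. Recruitment was ongoing and no interim analysis of the research questions is planned, so it can be made before outcomes are compared.

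The cost is power, and it should be disclosed. At the first Holm step, 398 mothers give about .50 (two-sided) or .60 (one-sided) for d = .25 without baseline gain. Two-sided power is about .73 if the T1 correlation is .6. It is about .97 to .99 if the moderate effect means d = .5, with 318 to 398 mothers. Without baseline gain, .80 power at one-sided .0125 for d = .25 would need about 610 mothers. Making T4 primary is a design choice for the investigators. It is suggested because only T4 follows both visits.
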